**Figure 1 figure1:**
[figure not shown]
Diagram detailing the timeline for the study components. QoL: quality of life; CPQ-12: Computer Proficiency Questionnaire-12; SI scale: social isolation scales (Center for Epidemiologic Studies Depression Scale and University of California, Los Angeles Loneliness Scale version 3).

### Outcomes

*Primary outcomes:* The primary outcomes of this study are loneliness and depression. Loneliness will be assessed using the UCLA Loneliness Scale-version 3 [43]. The scale is a 20-item measure using a 4-point Likert scale and has been validated for use with older adults [44]. Depression will be measured using the CES-D [45]; this is a 20-item scale, each with 4 response items ranked from 0 to 3 based on the frequency of symptoms associated with depression over the past week. A cut-off of over and equal to 16 has been used in multiple validation studies [46].

*Secondary outcomes*: The secondary outcomes of this study are quality of life and computer proficiency. Quality of life will be measured using the OPQOL-Brief and a 13-item Likert scale from 1 to 5. This scale has been validated in older adults [47]. Technological proficiency will be measured using the CPQ-12, a 12-item measure using a 1-5 Likert scale and has been well-studied in older adults [48].

*Feasibility outcomes:* The feasibility outcome measures of this study will include the number of participants that we are able to enroll in the study, adherence to the intervention (frequency of contact with the family and attendance to the program), and the rate of attrition [49]. We also intend to determine the challenges faced by the site and volunteers as a result of our intervention, in particular, the restrictions of having only university student volunteers as well as the restrictions of the daily schedules for the residents of the facility. These will both be determined quantitatively (eg, total number of participants, adherence) and qualitatively, where participants will be asked about their experiences with the program. We do not expect any adverse events as a result of our intervention.

*Qualitative interviews:* Semistructured interviews will be conducted with older adults prior to and following the 8-week intervention. Interviews will be continued with all the participants before the study and those in the intervention condition after the study has concluded. Interviews will be digitally audio recorded and transcribed verbatim, and pseudonyms will be assigned to participants. A thematic analysis methodology will be used to code the qualitative data. Two independent investigators will conduct line-by-line coding. The preintervention and postintervention questionnaires are provided in Multimedia Appendix 7 and Multimedia Appendix 8, respectively. Qualitative interviews will provide context in the role that the enTECH program provides for older adults living in long-term care facilities as well as how they currently socialize with others. By assessing participants both before and after the intervention, we hope to provide narrative data on how the enTECH program may have changed the way participants socialize in their community, determined changes in their knowledge with technology, and provided insight into their experience with the program. In addition, by understanding the goals participants have by enrolling in the program, future modifications to the program may allow for more tailored technology and social interventions.

### Statistical Analysis

#### Statistical Software

Participant demographic data will be tabulated for both intervention and control groups with their respective means and standard deviations. Participant dropouts will also be considered, and an intent-to-treat analysis will be completed. All data will be analyzed using GraphPad Prism 9 (GraphPad Software, Inc).

#### Primary Outcomes

The UCLA Loneliness Scale and the CES-D Scale will be analyzed using a repeated measures approach, as these measures will be collected weekly. The normality of the data will be assessed using the Shapiro-Wilk test; if the data are nonparametric, a Q-Q plot will be performed to identify skewness of the data. A Brown-Forsythe test will be used to determine equal variance. If the data are determined to be normally distributed and equal variance is observed between the groups, a repeated measures analysis of variance test will be used to detect between-group and within-group differences. If normality cannot be established or unequal variance is observed within the data, the Friedman test will be used to detect between-group and within-group differences. If the data are nonnormal with unequal variance, a Box-Cox transformation will be performed to obtain equal variances. For all tests, statistical significance will be set at *P*<.05.

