#### Participant Recruitment

Participants will be recruited through a long-term care home in Southern Ontario. Recreational facilitators will assist in recruiting participants for the study. Moreover, brochures, pamphlets, and flyers (Multimedia Appendix 2) will be placed in the study location by the team, in addition to a town hall advertising the study. Potential participants will be asked 2 questions to determine eligibility: if they currently use email/texting/messaging to contact family members and if they believe a family member would be willing to respond to an email sent by them once a week (Multimedia Appendix 3). Collecting the contact information of the participants’ family members requires balancing of respect for the participants’ autonomy, along with their potential comfort with the study’s subject matter. After consenting, participants will be presented with 2 options so that the research team can contact their family members. One option will consist of the participant providing the research team with a ranked list of family members to potentially receive emails from the participant, along with their phone numbers. The other option will consist of providing the participants with an information sheet, written in layperson terms, which they can use to describe the study to the family members to ask if they would like to participate. Members of the research team will follow up after 3 days to see if the participants were able to contact their family members or to provide support to facilitate this contact. The research team will then offer to contact the family member on their behalf, and at such time will record the contact information of up to 3 family members and contact them using the telephone script (Multimedia Appendix 4). Recruitment for the study started in November 2019. We expected to enroll approximately 20 participants, 10 in each condition. We successfully enrolled 8 participants before the study was forced to halt due to the COVID-19 pandemic (Multimedia Appendix 5).

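### Significance pre-tests on the outcome data choose the primary analysis, so chance alone can move an outcome from repeated-measures ANOVA to a Friedman test that does not compare the arms

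*Protocol article*

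**What the plan says.** The Outcomes section names two primary outcomes: "The primary outcomes of this study are loneliness and depression". Both scales are scored weekly in both arms.

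Under Primary Outcomes in Statistical Analysis, the method for each scale follows from tests on the trial data:

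- Normality: "The normality of the data will be assessed using the Shapiro-Wilk test".
- Variance: "A Brown-Forsythe test will be used to determine equal variance".
- Both passed: the condition is "If the data are determined to be normally distributed and equal variance is observed between the groups", and repeated-measures ANOVA is then used.
- Either failed: "If normality cannot be established or unequal variance is observed within the data, the Friedman test will be used". The article gives it the task of finding both between-group and within-group differences.
- Both failed: "If the data are nonnormal with unequal variance, a Box-Cox transformation will be performed to obtain equal variances".

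The threshold is common to everything: "For all tests, statistical significance will be set at" P<.05. The section does not say whether the pre-tests apply to each arm and week, to pooled scores or to residuals. It also does not say what follows when weeks, arms or scales disagree. Under Participant Recruitment, the size is given as "We expected to enroll approximately 20 participants, 10 in each condition".

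**The concern.** A pre-test at the 5% level rejects sound data some of the time. Repeated over weeks and arms, or applied to pooled scores that are not independent, it rejects far more often. Here a rejection changes the primary analysis, and it changes it to something that answers a different question. The Friedman test ranks each participant's scores across weeks. It has no factor for arm, so it cannot compare intervention with control, whatever task the article assigns to it.

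The branches also collide. When both pre-tests fail, the Friedman rule (normality or variance fails) and the Box-Cox rule (both fail) apply together, and nothing says which prevails or which test follows the transformation.

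At stake is whether the randomised comparison on loneliness and depression is reported at all, and whether both scales are analysed the same way.

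**Working it through.** The plan gives no figure for how this rule behaves, so there is none to reproduce.

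**Inputs from the protocol article.** 10 per arm (Participant Recruitment). Eight scores per person: weeks 1-7 plus week 8 (enTECH Intervention and Study Procedure). Two primary outcomes (Outcomes). Pre-tests at 0.05 (Primary Outcomes). Planning effect size 0.2 (Power).

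**Assumed.** Within-person correlation, which the article does not give: 0.5, 0.7 and 0.9, with some runs at 0.8. Data are exactly normal with equal variances, so every rejection is a chance rejection. One rejection is taken to divert the outcome.

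**Step 1: number of tests.** Testing per arm and week gives 2 × 8 = 16 Shapiro-Wilk and 8 Brown-Forsythe tests, 24 per scale. If the tests were independent, the chance of at least one rejection among k is 1 − 0.95^k:

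- k = 2: 1 − 0.95² = 9.8%
- k = 16: 1 − 0.95¹⁶ = 56%
- k = 24: 1 − 0.95²⁴ = 71%

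Weekly scores are correlated, and Brown-Forsythe rejects only about 3.6% of the time at 10 per arm, so the true figure for 24 tests is somewhat lower. Pooling weeks has a different fault: 80 values per arm come from 10 people but are treated as independent.

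**Step 2: simulated chance diversion, one scale, no effect.** Ranges span separate simulation runs.

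| What is tested | Correlation 0.5 | 0.7 | 0.9 |
|---|---|---|---|
| Each arm and week (16 + 8 tests) | 65-66% | 62-66% | 48-52% |
| Weeks pooled within arm (2 + 1 tests) | 35-38% | 61% | 92-95% |
| One residual test, one variance test on person means | 8.8% | 7.5% | 8.1% |

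Runs at correlations 0.5 and 0.8 add two further readings: arms pooled within each week, 50.7% and 39.4%; all person-weeks pooled, 29.8% and 65.1%. For the residual reading, all runs together lie between about 7% and 11%. With 4 per arm (the 8 enrolled before the halt, if split evenly), testing per arm and week diverts 75.4% and 70.6%.

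**Step 3: does the gate catch real departures?** With 10 values, Shapiro-Wilk detects clear skewness (chi-square, 4 df) in only 24% of samples. At this size it is a weak detector of the problem it is meant to find.

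**Step 4: different methods for the two scales.** If each scale is diverted with probability p, and independently, the methods differ with probability 2p(1 − p):

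- p = 0.50: 2 × 0.50 × 0.50 = 50%
- p = 0.65: 2 × 0.65 × 0.35 = 45.5%
- p = 0.08: 2 × 0.08 × 0.92 = 14.7%

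Loneliness and depression scores are probably correlated, which would lower these.

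**Step 5: cost to the arm comparison.** Take a 1 SD effect for illustration. A fixed between-arm t test on person means is significant in 80%, 68% and 60% of trials at correlations 0.5, 0.7 and 0.9. Under the rule with tests per arm and week, only undiverted trials yield an arm comparison. Treating passing and detection as independent:

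- (1 − 0.66) × 0.80 = 27%
- (1 − 0.62) × 0.68 = 26%
- (1 − 0.52) × 0.60 = 29%

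Direct simulation gave about 24-29%.

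**The case against.** **The unit is not stated.** The large percentages depend on testing raw scores by week or pooled. If the team means one residual test and one variance test on person means, diversion is only about 7-11%. A condensed article may leave the unit to a fuller document. This stands as a limit on the size, and the missing unit alone is not the fault. The rule that a failed pre-test replaces the primary analysis is stated in the article and is a fault on any reading.

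**A reader might infer that a real effect makes diversion more likely.** The figures do not support this in general. Tests within arm, and the median-centred Brown-Forsythe test, are unaffected by a constant shift between arms. Per arm and week at correlation 0.8, diversion is 57.0% with no effect, 60.1% at 0.2 SD and 57.3% at 1 SD, which is flat within simulation error of 1-2 points. A rise needs one Shapiro-Wilk on all 160 raw scores and a large shift: at correlation 0.7, 28.8% with no effect, 27.6% at 0.2, 35.9% at 1 SD and 63% at 2 SD. The article plans for 0.2.

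**A reader might also infer that the gate inflates type I error.** With a sound fallback (Mann-Whitney on person means) it does not. Error was 4.3%, 4.9% and 4.2% at correlations 0.5, 0.7 and 0.9, against 5.1%, 5.4% and 4.5% for the t test alone. Power at 1 SD was 77%, 65% and 58%, a loss of 2-3 points. The serious harm therefore comes from the gate together with the fallback it leads to.

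**This is a feasibility trial, and assumption checks are conventional.** That lowers the stakes. But the article states a hypothesis of benefit, names these two scales as primary, sets P<.05 and intends the trial to guide a later one.

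**Conclusion.** The point holds with limits. A stated rule lets chance help decide whether each primary outcome gets an analysis that compares the arms. With 10 per arm, eight weekly scores and sound data, chance diversion is about 50-65% per scale for tests per arm and week, about 35-95% with weeks pooled within arm, and about 7-11% for a single residual test plus a single variance test. These rest on the assumed correlations of 0.5-0.9 and on one rejection being enough to divert.

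The consequences are a method chosen by noise, possibly different methods for the two scales, and loss of the randomised comparison for any scale sent to Friedman. It should be corrected before analysis. The trial is halted, so there is time.

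**What to change.** Under Primary Outcomes, delete the rule that Shapiro-Wilk and Brown-Forsythe results choose the test, together with the Friedman and Box-Cox branches that depend on it. Name one primary analysis for both scales:

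- A repeated-measures model with arm, week and arm-by-week, and participant as the repeated unit.
- The arm contrast that counts as the result, stated in advance (for example the mean difference over the eight weeks, or the difference at week 8; the team must pick one).
- Residual plots reported as description only, with no effect on the choice of method.
- A P value from permuting the arm labels as the pre-stated sensitivity analysis. It does not rely on normality.

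Under Secondary Outcomes, name one between-arm test of change for quality of life and computer proficiency, in place of a list from which diagnostics choose.

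The cost is a change of wording and a little more analysis work. The permutation P value needs a few lines of code outside the named software. No new data are needed.

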### enTECH Intervention and Study Procedure

After obtaining informed consent, demographic information will be collected (Multimedia Appendix 6) and participants will be randomized as described above. The intervention outline is described below and detailed in the study flow chart of Figure 1.

*Week 0*: Members of the study team will conduct semistructured interviews with participants (Multimedia Appendix 7) and complete the Computer Proficiency Questionnaire-12 (CPQ-12) and the Older People’s Quality of Life-Brief version (OPQOL-Brief) questionnaire, which will be measured before and after the study period.

*Weeks 1-7:* Participants in the intervention group will complete the enTECH program. Trained enTECH volunteers will help older adults use either our laptops or participants’ own technology systems to email their family members. These sessions will take place in group settings in a public area in the long-term care facility accessible to all participants. Both the Center for Epidemiologic Studies Depression scale (CES-D) and the UCLA (University of California, Los Angeles) Loneliness Scale (version 3) will be measured each week in the intervention and control groups.

*Week 8:* Participants in both groups will complete their final session of the intervention, and they will then be asked to complete the CPQ-12, the OPQOL-Brief, the CES-D, and the UCLA loneliness scale. Participants in the intervention group will also be invited to complete a second interview discussing their experiences using technology to communicate with a family member (Multimedia Appendix 8).

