#### Power

This study was designed as a feasibility study for investigating the feasibility of a student-run initiative to reduce loneliness in older adults. A component of this study will be understanding recruitment and retention, which may have significant variability in our sample size. Based on previous studies on interventions to reduce loneliness in older adults, with an effect size of approximately 0.2 and alpha of .05 and 80% power, we expect our sample size to be 196 [43,50-54]. Accounting for attrition rates in other intergenerational programs would be approximately 10%, and the sample size would be 216 [20,55,56]. Since the nature of this study is a feasibility study, which we aim to use to guide a future randomized controlled trial, this feasibility trial is not registered.

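### The tests named for the weekly primary outcomes need a complete eight-week series, which does not fit the promised intent-to-treat analysis, and the conditions for the ANOVA omit sphericity

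*Protocol article*

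**What the plan says.** Under Statistical Analysis, Primary Outcomes, the article fixes two routes for both primary outcomes. The first opens with the conditions "If the data are determined to be normally distributed and equal variance is observed between the groups"; when they are met, "a repeated measures analysis of variance test will be used to detect between-group and within-group differences". Otherwise "the Friedman test will be used to detect between-group and within-group differences". Each test is judged at P<.05.

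The Statistical Software paragraph adds: "Participant dropouts will also be considered, and an intent-to-treat analysis will be completed". It names the package but no settings and no method for missing scores.

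The section enTECH Intervention and Study Procedure sets the occasions. In Weeks 1-7 the two scales "will be measured each week in the intervention and control groups", and at Week 8 "they will then be asked to complete the CPQ-12, the OPQOL-Brief, the CES-D, and the UCLA loneliness scale". That makes eight scores per participant on each primary scale. Neither scale is listed at Week 0.

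Participant Recruitment gives a target of about 20, with 10 per arm. Power expects attrition of about 10%.

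**The concern.** There are two separate problems.

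**Who is analysed.** Classical repeated-measures ANOVA and the Friedman test both need a full row of scores from each participant. A resident who leaves at Week 5, or who misses a single week, drops out of the calculation altogether. The outcome is then a complete-case analysis. In a long-term care population, a missed week could plausibly go with low mood or poor health, which are close to what is being measured. The documents give no data on this. If it happens, the arm comparison may be biased as well as less precise.

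**Which assumptions are checked.** The conditions leading to the ANOVA cover distribution shape and variance across arms. They leave out the assumption particular to repeated measures, namely that differences between all pairs of weeks have the same variance (sphericity). Scores taken a week apart usually correlate more strongly when they are closer in time, and that breaks sphericity. The F tests for week and for arm-by-week then reject too often unless their degrees of freedom are reduced. The arm-by-week term matters because it shows whether the arms change differently over time.

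**Working it through.** **Inputs from the article.** Eight scoring occasions (7 weekly plus Week 8); 20 participants, 10 per arm, 1:1; attrition about 10%; alpha .05.

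**The plan's own figures.** Power states "with an effect size of approximately 0.2 and alpha of .05 and 80% power, we expect our sample size to be 196". With (1.960 + 0.842)² = 7.849, 7.849 / 0.2² = 196.2, so 196 reproduces. Adding 10% gives 196 × 1.10 = 215.6, the stated 216. Neither figure uses a repeated-measures formula, so they do not bear on this point beyond supplying the attrition rate.

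**Step 1: participants with a complete series.** Let d be the dropout proportion and m the chance of missing any one weekly score, independent across weeks. Then P(complete) = (1 − d)(1 − m)^8. The article gives d = 0.10; the values of m are assumptions.

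| m | (1 − m)^8 | × 0.90 | of 20 |
|---|---|---|---|
| 0 | 1.000 | 0.900 | 18.0 |
| 0.02 | 0.851 | 0.766 | 15.3 |
| 0.05 | 0.663 | 0.597 | 11.9 |
| 0.10 | 0.430 | 0.387 | 7.7 |

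**Step 2: type I error of the uncorrected tests.** Null trials were simulated with 10 per arm, 8 weeks and complete data, 20,000 per scenario. The Monte Carlo standard error near 5% is √(0.05 × 0.95 / 20,000) = 0.15 percentage points. The correlations are assumptions; the article gives none.

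| Within-person correlation | Week | Arm-by-week | Arm main effect |
|---|---|---|---|
| Equal for all pairs, 0.5 | 5.2% | 5.0% | 4.9% |
| AR(1) 0.3 | 5.7% | 5.5% | 5.1% |
| AR(1) 0.5 | 7.2% | 7.5% | 5.1% |
| AR(1) 0.7 | 8.7% | 9.2% | 4.8% |
| AR(1) 0.9 | 11.0% | 10.8% | 5.2% |

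Giving half of the variance to a stable person effect and the rest to an AR(1) process hardly changes this: the arm-by-week rate is 7.1% at 0.5 and 8.9% at 0.7.

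**Step 3: effect of a correction.** With Greenhouse-Geisser, the week and arm-by-week tests reject 3.0% to 4.8% of the time across the same scenarios. With 4 per arm (the 8 recruited so far, if evenly split), the uncorrected arm-by-week rate under AR(1) 0.3 to 0.9 is 5.9% to 11.1%. The corrected tests are then conservative, at about 1% to 4%.

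**The case against.** The strongest reply is that the article is silent on these points and does not state an error. It says that dropouts will be considered and nowhere says that incomplete participants will be removed. Imputation before the ANOVA, or a likelihood-based repeated-measures model, would reconcile the two statements. Both the missing-data method and an epsilon correction are details often left to an analysis plan, which is not shown. This part stands: a reader might infer that the plan contradicts itself or intends to discard residents with a missed week, and the text supports neither. What remains is that the article does name its tests, and neither named test, used in its ordinary form, can include everyone randomised once any score is missing.

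A reader might also infer that the false-positive rate is inflated as a matter of fact. The documents do not support that. Inflation needs both non-sphericity and no correction, and the article neither gives correlations nor rules a correction out. With equal correlation between all weeks the rate is about 5%.

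Nor does the mention of within-group differences show that change inside one arm will be read as efficacy. It may only describe the within-subject terms of the model.

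Finally, the losses beyond 18 of 20 rest on assumed weekly rates, and this is a feasibility trial that itself expects difficulty in reaching significance. That limits the consequence. The trial nevertheless plans significance tests on both primary outcomes and intends to guide a later randomised trial.

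**Conclusion.** The point holds as an incompatibility between the named tests and the promised analysis set, together with an incomplete list of conditions for the ANOVA. It should be put right before the trial restarts.

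On the plan's own attrition, about 18 of 20 participants would have a complete series. Under assumed independent weekly losses of 2%, 5% or 10%, that falls to about 15, 12 or 8. If weekly scores follow AR(1) correlation of 0.3 to 0.9 and no correction is applied, the week and arm-by-week tests run at about 5.5% to 11% instead of 5%. The between-arm main effect stays at its nominal level throughout, so the sphericity problem does not touch a comparison of the arms averaged over weeks. The loss of incomplete participants affects every term.

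**What to change.** Replace both the ANOVA and the Friedman fallback with one REML linear mixed model per scale, using all available weekly scores from every randomised participant:

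- fixed effects for arm, week and arm-by-week;
- a parsimonious serial covariance, such as AR(1) plus a random intercept. An unstructured 8 × 8 matrix has 8 × 9 / 2 = 36 parameters, too many for about 20 participants;
- small-sample degrees of freedom;
- one between-arm contrast named in advance as the treatment effect, either at Week 8 or averaged over weeks;
- within-arm change reported descriptively only.

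Do not include a Week 0 covariate unless the UCLA and CES-D scales are actually collected then, which the procedure section does not list. State that the model relies on missing scores being missing at random, and that a participant with no weekly score contributes nothing to it.

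If the ANOVA is kept, state a missing-data method that retains all randomised participants and apply a Greenhouse-Geisser correction to the week and arm-by-week tests.

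The cost is revised analysis wording, a somewhat more complex analysis and possibly other software. No new data are needed. Recruitment is halted at 8 participants, so the change can be made before restart.
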